### Relevant concomitant care permitted or prohibited during the trial {11d}

While the standard-of-care for clinical management of malaria and vector control interventions (e.g., ITNs, IRS) will not be withheld in any of the distribution channels, these interventions will be monitored and recorded throughout the study. ITNs continue to be distributed through mass campaigns every 2 years with the latest distribution conducted in early December 2023 in Yumbe District, where the Bidibidi Refugee Settlement is located. ITNs are also distributed regularly to pregnant women during antenatal and postnatal care services at health facilities in the Bidibidi Refugee Settlement, and to children under five during expanded immunization programs. IRS started in December 2022 and is expected to occur annually, with the latest conducted in December 2023. At enrollment, eligible children will be provided a treatment dose of artemether-lumefantrine (AL) free of charge for malaria parasite clearance and a new ITN. In addition, study participants will be provided treatment for malaria infection throughout the follow-up period. Participants will be encouraged to continue ITN use and not instructed to avoid alternative vector control tools (e.g., coils, topicals, aerosol sprays, repellents) which will allow for an estimation of the SR effect assuming all other measures are still occurring for malaria prevention, essentially providing insight on an additive benefit above that provided by currently recommended WHO malaria preventive measures.

### Provisions for post-trial care {30}

Not applicable—the study will not provide post-trial care.

### Outcomes {12}

The primary outcome measure of this study will be the effectiveness of SR as measured by RDT confirmed malaria infection incidence (both first-time and recurrent), following the deployment of SR, between each of the two operational program delivery mechanisms (VHT and Voucher) versus the reference distribution channel.

Secondary outcome measures include:Cost-effectiveness of SR distribution by each distribution channel (VHT and Voucher) compared to the reference distribution channel.AEs and SAEs as measured by solicited and unsolicited reports during the intervention period (12 months). The mean, minimum, and maximum frequency and percentage of AEs and SAEs across clusters among enrolled participants will be summarized by distribution channels.

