## Introduction

### Background and rationale {6a}

Spatial repellents (SRs) are a promising new vector control paradigm that could add to the existing armamentarium for malaria prevention [1, 2]. SRs such as mosquito coils have been shown to reduce mosquito biting [3, 4]and, in studies conducted in Indonesia [5, 6] and China [7], to reduce malaria transmission in human populations. Recently, SRs have also been proven to reduce *Aede*s-borne viruses [8]. Although the value of SR is applicable across a wide range of scenarios, evidence is required to demonstrate the effectiveness of SRs under operational use conditions. One scenario in which SRs have potential for significant impact is in humanitarian relief efforts. People who have been displaced due to conflict or environmental disasters very often arrive in an exhausted, weakened, traumatized state, already suffering from or vulnerable to infectious diseases and malnutrition. They may lack access to health services and health commodities such as insecticide-treated nets (ITNs), and temporary structures to accommodate them are often substandard or semi-enclosed, providing little protection from mosquitoes.

As of 31 March 2023, the United Nations High Commissioner for Refugees has registered 1,532,168 refugees in Uganda, of which 867,391 are from South Sudan and 487,044 are from the Democratic Republic of Congo. Uganda has a unique refugee policy, whereby refugees are given a 30 × 30 plot to construct their structures and farm on this land. Refugees are placed into different areas based on their date of arrival. Refugees live among host communities in the same area and have equal access to health facilities and other services.

Malaria is highly endemic throughout all of Uganda and accounts for 31.1% (14,381,183/46,261,118) of all reported outpatient visits and 25% (844,965/3,385,664) of all admissions, placing a heavy burden on the health care system [9]. This is especially true in the north of the country, where fighting in South Sudan has displaced tens of thousands of South Sudanese people who have been forced to seek refuge in northern Uganda. The prevalence of malaria according to rapid diagnostic test (RDT) in all refugee settlements across the nine hosting districts was 36.6% for children 6–59 months [10]. Refugees live in grass thatched roof houses or in tarpaulin structures, and at times in areas of rapid over-growth that provide ample breeding space for mosquitoes.

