All children enrolled in the study will be provided an ITN. This will allow us to measure the added benefit of SR product above that provided by currently recommended preventive measures. In addition, a blood sample will be taken for a RDT for all participants enrolled in the cohort to be used as a baseline data measure. All participants (regardless of RDT results) will be provided a treatment dose of artemisinin-combination treatment (ACT) AL at the start of the study prior to receiving SR, to clear any prepatent or patent malaria parasites, unless they have recently been treated (within the last 2 weeks). Participants will be treated according to RDT results throughout the study period, according to national protocols.

The enrollment period will take approximately 1 month, during which time incidence of malaria disease in study clusters will be measured prior to the deployment of the study product.

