#### Follow-up of the cohort

All efforts to overlay the commencement of enrollment with the start of the malaria transmission season will occur; however, programmatic timelines may not allow for perfect alignment. The 12-month follow-up period will ensure estimating potential changes in malaria incidence during anticipated seasonal malaria transmission peaks.

The distribution of the SR will occur after enrollment. At this time, cohort participants will be presumptively cleared of parasites with a treatment dose of AL unless they have recently been treated (within the last 2 weeks). This will be done so that the incidence of malaria infection following study product deployment can be measured.

Participants enrolled in the cohort will be followed every 2 weeks for malaria infection during the 12-month period after the study product has been distributed. All cohort participants and HH residents will also be informed to come to the nearest health facility for unscheduled sick visits, as needed. If the participant presents with a history of fever in the last 48 h, a RDT will be performed and AL will be administered if the RDT is positive for malaria.

Every 2 weeks, study team data collectors will visit the enrolled HHs. At each data collection HH visit, the parent/guardian will be asked about the recent use of ITNs and other vector control interventions as well as recent history of illness, recent travels outside the HH, and recent use of anti-malarial drugs.

During the first scheduled HH visit, a blood sample will be taken for malaria RDT (Monthly Visit #1). During the second scheduled HH visit, a blood sample will only be taken if the participant has a recent history of fever (Monthly Visit #2). The total blood volume for samples at each visit will not exceed 500 mli. A second blood sample may be taken for hemoglobin testing during follow-up only if the data collection/clinical team suspects anemia in participating children.

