Cohort participants who test positive for malaria by RDT will be treated with ACTs free of charge according to national treatment guidelines. Hospital fees will not be paid by the study unless the illness or injury is due to study products or procedures as determined by the health facility physician and the study coordinator, in coordination with the study’s local PI. If there is illness or injury due to study products or procedures, fees will be paid for care at the government health facilities or District or Provincial Hospital according to the clinical trial insurance policy of the study.

When participants are not available for a follow-up visit, there will be a grace period/ “window” for each follow-up visit. There will be an allowable range of + / − 3 days for scheduled follow-up data collection home visits to occur.

In total, it is estimated that approximately 2.5 h will be needed from research participants at the start of the study (for the HH mapping, structures and HH enrollment, parasite clearance, and distribution of ITN). Throughout the study, 50 min will be needed for the VHT and study personnel arms (for the follow-up visits and SR placement), while approximately 1 h may be needed for the voucher arm as they will be walking to the central location to redeem their SR.

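### Clearance after treatment is never confirmed by a test, so positives persisting from baseline can count as new infections and pull a non-null HR toward 1

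*Protocol article*

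**What the plan says.** Outcomes {12} defines the primary outcome as the "effectiveness of SR as measured by RDT confirmed malaria infection incidence (both first-time and recurrent), following the deployment of SR".

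Clearance is handled by treatment. Enrollment of the cohort states: "All participants (regardless of RDT results) will be provided a treatment dose of artemisinin-combination treatment (ACT) AL at the start of the study", before the SR, with an exemption for children treated in the previous 2 weeks. Follow-up of the cohort gives the reason: "This will be done so that the incidence of malaria infection following study product deployment can be measured". For later positives: "Cohort participants who test positive for malaria by RDT will be treated with ACTs free of charge according to national treatment guidelines".

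Testing is by RDT for every child at Monthly Visit #1 and, at Visit #2, only after recent fever. A baseline RDT is taken from all children. Background and rationale {6a} gives the only prevalence figure: "The prevalence of malaria according to rapid diagnostic test (RDT) in all refugee settlements across the nine hosting districts was 36.6" per cent, in children of 6 to 59 months.

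None of these sections, nor the models in Statistical methods {20a}, nor the incidence-rate calculation in Methods for additional analyses {20b}, requires a negative RDT after treatment, sets a period not at risk, or separates a recurrence from a persisting positive.

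The timing of AL is worded in three ways. Relevant concomitant care {11d} places it at enrolment. Enrollment of the cohort places it at the start of the study, before the SR, and says that enrolment takes about 1 month. Follow-up of the cohort says "The distribution of the SR will occur after enrollment" and then places clearance at this time, which can refer to either event.

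**The concern.** An outcome based on any positive RDT after deployment measures new infection only if the child was test-negative when time at risk began. The plan assumes this after treatment and does not check it. A child who was positive at baseline and is still positive at the first monthly test would be recorded as a first infection after the SR, and would leave the first-infection risk set at that visit.

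Such events owe nothing to the delivery channel. They add the same amount to each arm and so dilute a real difference. The direction matters because the trial makes no formal test (Sample size {14}) and is meant to inform equivalence of impact across delivery systems (Background and rationale {6a}). An HR pulled toward 1 is the reassuring error.

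**Working it through.** **Inputs from the protocol.** 16 clusters per arm, 40 households per cluster, between-cluster CV 0.40, 10% loss, 12 months, 0.5 to 1.0 infections per person-year (Sample size {14}); 90% Wald interval (Statistical methods {20a}); prevalence 36.6% (Background {6a}).

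**Assumed, not in the protocol.** f, the share of baseline positives still RDT-positive at the first monthly test: 0.1 to 0.5. q, the chance that a treated follow-up episode is still positive at the next monthly test: 0.25 to 0.75.

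**1. The plan's precision figure.** First events per cluster: e = 40 × 0.9 × (1 − exp(−rate)), which is 14.16 at 0.5 and 22.76 at 1.0. SE(log HR) = √[(2/16)(1/e + 0.40²)] = 0.170 and 0.160. Then exp(±1.645 × SE) gives 0.756 to 1.322 at 0.5 and 0.769 to 1.300 at 1.0. This agrees with the stated lower bounds of 0.77 to 0.75 and upper bounds of 1.30 to 1.33; the wider interval belongs to the lower rate.

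**2. Baseline carry-over, first-time endpoint.** Take 12 monthly intervals, with h = rate/12 in the reference arm and HR × h in the other. Carry-over is c = 0.366 × f: 3.7% of children at f = 0.1 and 18.3% at f = 0.5. True first-month infections are 1 − exp(−h): 4.1% at 0.5 and 8.0% at 1.0. The chance of an event in interval 1 becomes 1 − (1 − c)exp(−h) in each arm, and later intervals are unchanged. The expected counts were fitted by a cloglog model with a free intercept per month, without cluster effects or dropout.

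The mechanism shows in interval 1 at rate 0.5, f = 0.5. Carry-over adds −log(1 − 0.183) = 0.202 to both hazards, so their ratio is (0.0542 + 0.2021)/(0.0417 + 0.2021) = 1.05 instead of 1.30. Over 12 months, a true HR of 1.30 is estimated as:

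| f | rate 0.5 | rate 1.0 |
|---|---|---|
| 0.1 | 1.273 | 1.283 |
| 0.3 | 1.228 | 1.251 |
| 0.5 | 1.192 | 1.222 |

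- At f = 0.5 a true 1.50 reads as 1.32 (rate 0.5) or 1.37 (rate 1.0). A true 1.00 stays 1.00.
- Leaving out interval 1 returns 1.30 and 1.50, so the bias sits in that interval.
- Against the SEs of step 1, the shift from 1.30 is log(1.30/1.273)/0.170 = 0.12 SE to log(1.30/1.192)/0.170 = 0.51 SE at rate 0.5, and 0.08 to 0.39 SE at rate 1.0.
- At f = 0.5, carry-over is 0.183/[1 − 0.817 × exp(−rate)] of reference-arm first events: 36% at 0.5 and 26% at 1.0.
- For the overall endpoint, baseline carry-over alone at f = 0.5 turns 1.30 into 1.22 (rate 0.5) or 1.25 (rate 1.0).

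**3. Carry-over from a treated follow-up episode.** That child has already had a first infection, so only the overall endpoint is exposed. With p = 1 − exp(−h), the hazard in months 2 to 12 becomes h − log(1 − qp), and the added part follows each arm's own episodes. At rate 1.0, q = 0.75: reference 0.0833 + 0.0618 = 0.1452; other arm 0.1083 + 0.0801 = 0.1885; ratio 1.298. Over q = 0.25 to 0.75 and both rates, a true 1.30 reads as 1.297 to 1.299 and a true 1.50 as 1.495 to 1.498. The reference-arm rate is multiplied by about 1 + q × (11/12) × exp(−h), an inflation of 21% (q = 0.25, rate 1.0) to 66% (q = 0.75, rate 0.5).

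**4. A gap between AL and SR.** If g months pass between them, infections acquired in the gap add g × rate/12 to the interval 1 hazard in both arms. For g of 0.5 to 1 month this is 2% to 8% of children, and a true 1.30 reads as about 1.28 to 1.26.

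**5. Entry at the first negative RDT.** Under the model of step 2, without child-level frailty, this rule returned 1.30 in every scenario.

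**The case against.** - **The SAP may hold the rule.** At-risk windows often sit there, the article says a SAP exists, and it is not shown. This stands as a limit on severity. The point remains because what counts as an event is part of the primary outcome, and the outcome as stated here would count persisting positives.
- **The plan does clear parasites.** A reader might infer that there is no clearance rule at all. The protocol does not support that: AL goes to nearly all children whatever their RDT result, and follow-up positives are treated. What is missing is confirmation by test and a rule for a repeat positive.
- **Treated episodes.** A reader might also infer that persisting positives after a treated episode enter both endpoints and dilute both HRs. They cannot enter the first-time endpoint, and step 3 shows almost no effect on the overall HR.
- **The size rests on f.** No section says how long an RDT stays positive after treatment, or which RDT is used. The 36.6% covers settlements in nine districts. The cohort comes from Zones 1 to 4 of one settlement, with 30% host-community clusters, after ITN distribution and IRS in December 2023. This stands: the figures are scenarios, and at f = 0.1 the shift is small beside the planned interval.
- **AL timing.** The three passages can all be read as AL at enrolment followed by the SR, so they are ambiguous and not plainly contradictory. Infections acquired in a gap would be real ones, though acquired before the SR.
- **The remedy could select by arm.** Entry depends on a negative RDT after deployment, which the channel can influence. Step 5 shows no resulting bias in a model without frailty; with strong differences in risk between children, some selection could remain.

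**Conclusion.** The point holds in a limited form. The protocol treats before deployment but never confirms clearance, and it does not say when a positive RDT after treatment is a new infection. Baseline carry-over would then attenuate a non-null HR in both endpoints. For first infections, a true 1.30 reads as about 1.27 to 1.19 at 0.5 per person-year and 1.28 to 1.22 at 1.0, which is roughly 0.1 to 0.5 of a standard error. This rests on f of 0.1 to 0.5, the 36.6% proxy and equal carry-over across arms. There is no bias if the true HR is 1.

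Positives persisting after treated follow-up episodes are a matter for the absolute overall incidence rates, which could feed the cost-effectiveness work, and not for the HR. Severity is low to moderate.

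**What to change.** Define at-risk time with the RDTs already scheduled:

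- A child RDT-negative at baseline enters at SR deployment.
- A child RDT-positive at baseline enters at the first negative RDT after AL.
- After a treated positive, a child re-enters the recurrent endpoint only after a negative RDT.
- Positives before entry or re-entry are not events, and that time is not at risk.

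Keep the count-every-positive analysis as a sensitivity analysis. Reconcile the passages on AL timing relative to enrolment and SR distribution (Relevant concomitant care {11d}, Enrollment of the cohort, Follow-up of the cohort). If the SAP already holds such a rule, state it in the outcome definition.

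The cost is a written rule and some programming, with no new visits or tests. Some true early reinfections and some person-time are given up.

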### Participant timeline {13}

**Table Taba:** 

	**Study period**						
Timepoint	**Q3 2023**	**Q4 2023**	**Q1 2024**	**Q2 2024**	**Q3 2024**	**Q4 2024**	**Q1 2025**
Ramp up phase							
Census and mapping		**X**	**X**				
Intervention							
Allocation			**X**				
Informed consent			**X**				
Screening			**X**				
Follow-up				**X**	**X**	**X**	**X**
Assessment							
Final analysis							**X**

### Sample size {14}

The sample size of the number of clusters and the number of HHs per cluster is based on the assumption of a 40% between-cluster coefficient of variance; a 12-month intervention period; and a 10% loss to follow-up. Since the primary objective is to quantify the difference in effectiveness between each of the two real-life distribution channels and the reference without formal hypothesis testing, we focus on determining a practically feasible sample size that yields a satisfactory precision for the intervention comparisons on the malaria incidence rate. The previous data suggests that the baseline incidence rate in the study area is around 0.5 to 1 per person-year. Figure 1 provides the precision around the intervention comparison at different numbers of clusters and HHs per cluster. When the number of clusters is 16 per arm and the number of HHs per cluster is 40, the upper bound of the CI for the hazard rate (HR) between a real-life delivery system vs. the reference ranges from 1.30 to 1.33 for baseline HR of 0.5 to 1.0 per person year, and the corresponding lower bound ranges from 0.77 to 0.75 if the estimated HR is 1. Further increasing the number of clusters or the number of HHs per cluster does not significantly shorten the CI width and increase the precision of the HR estimation. Given the precision analysis for different sample sizes, we will recruit 16 clusters with 45 HHs per cluster for each of the 3 intervention arms; altogether, 2160 HHs will be recruited.

**Fig. 1 Fig1:**
[figure not shown]
The precision around the intervention comparison at different numbers of clusters and HHs per cluster

### Recruitment {15}

Prior to recruitment mapping will be conducted to obtain demographic details of HH members in each of the 48 clusters. Information regarding the study will be provided during the stakeholder and community leaders’ inception meetings through study personnel and VHTs, targeting parent(s)/ guardian(s) of potential participants in the community, community leaders, and organizations working with refugees and host communities. Information will be provided through community meetings held at local venues, brochures posters at health facilities and community meeting venues with study staff contact information (in English, Juba Arabic, Kakwa, Lugwara-Ti), study staff attendance at sponsored opinion and religious leaders’ meetings, women groups and men groups, and engagement with tribal and government leaders in the settlement area.

## Assignment of interventions: allocation

### Sequence generation {16a}

The unit of randomization for the SR intervention delivery channel will be a cluster. The study statistician will have access to malaria prevalence and census data that will be collected during the ramp-up phase of the study and may be used to inform potential stratification prior to randomization. Criteria for stratification will be malaria prevalence levels and/or demographic endpoints. Following stratification (as needed), clusters will be allocated to receive the SR product either through delivery by study personnel (reference arm, positive control), VHTs, or vouchers using a random number generator (https://www.random.org). The cluster allocation code will be made available to the DSMB for use in safety assessments. The site database manager will assign a unique HH identification number (HIN) to each HH for use in monitoring malaria infections during the trial and the site intervention administrator will coordinate SR product distribution to mitigate stock-out. Following cluster allocation, a total of 45 households will be randomly selected per cluster. In HHs with multiple children that meet the study inclusion criteria, all eligible children will be invited to participate; however, only one will be enrolled. The methods used for this randomization will be the rand() function from Excel for households and the random.sample() function for age-eligible members.

### Concealment mechanism {16b}

The Sponsor, study Principal Investigator (PI), and staff will not be blinded to cluster assignment (SR delivery channel). There will be no placebo integrated into the study design, as the SR intervention will have already been evaluated for efficacy under controlled conditions. Ethical approvals and census and mapping activities were conducted prior to the allocation. However, cluster allocation was shared with the study team prior to recruitment and enrollment to allow the identification of distribution points within clusters in the voucher arm and the recruitment of VHTs within the VHT arm.

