## Assignment of interventions: blinding

### Who will be blinded {17a}

The Sponsor, study PI, and staff will not be blinded to cluster assignment (SR delivery channel). There will be no placebo integrated into the study design, as the SR intervention will have already been evaluated for efficacy under controlled conditions.

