#### Enrollment of the cohort

A cohort of children aged ≥ 6 months to ≤ 59 months will be enrolled within each cluster to assess the effectiveness of the SR product against the contemporaneous control and in additional clusters to estimate effectiveness using programmatic delivery systems. HHs will be randomly selected from the master list of HHs obtained during ramp-up phase mapping to achieve the desired sample size.

Selected HHs based on cluster maps will be visited and if a child is present, the study will be explained and consent obtained from the child’s primary caregiver before screening for eligibility and enrolling him/her in the study. All eligible children in a selected HH will be invited to participate. (See above for a more complete description of the consent process.) At enrollment, the study team will have a list of all age-eligible children in each HH selected. These data will have come from the initial mapping and census of the study clusters. At the time of participant recruitment, the tablet will randomly select one of the age-eligible children for the field staff to screen for inclusion and exclusion criteria, which includes a hemoglobin test. Prior to screening, the team will obtain parental/caregiver consent. If there are no eligible children in the HH after screening, a new HH will be randomly selected from the HH listing exercise (mapping and census).

At enrollment, the age and gender of the child will be recorded and the parent/guardian (as needed) will be asked about the use of ITNs and anti-malarial drugs. Contact information, as available, will be captured. A fingerstick blood sample will be taken for a malaria RDT, and a hemoglobin level will be evaluated in a capillary sample using the HemoCue device**.** The study team will work with local health partners and the district health department providing iCCM to make sure children in need of iron supplements and antihelminths are managed according to national protocols and coordinate any referrals or follow-ups as needed. If the screened child does not meet the inclusion criteria, the tablet will randomly select another child from the remaining age-eligible children in the same house. The process will continue until one of the children is successfully enrolled.

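### Households are drawn and recruited after each cluster's delivery channel is known to the study team, so consent, contact effort and eligibility judgements can depend on the arm

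*Protocol article*

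**What the plan says.** The order of events is spread over several sections of the protocol article.

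- **Listing before allocation.** Concealment mechanism {16b}: "Ethical approvals and census and mapping activities were conducted prior to the allocation". The mapping section also places random allocation of clusters after mapping.
- **Household draw after allocation.** Sequence generation {16a}: "Following cluster allocation, a total of 45 households will be randomly selected per cluster". The tool named is the "rand() function from Excel for households".
- **Disclosure before recruitment.** Concealment mechanism {16b}: "cluster allocation was shared with the study team prior to recruitment and enrollment to allow the identification of distribution points within clusters". This purpose applies to voucher clusters. The other purpose given is to recruit VHT members for the VHT arm. Section {17a} confirms that sponsor, investigator and staff are unblinded.
- **Approach and replacement.** Enrollment of the cohort: "Selected HHs based on cluster maps will be visited and if a child is present, the study will be explained and consent obtained". If screening finds no eligible child, "a new HH will be randomly selected from the HH listing exercise (mapping and census". The tablet picks the child at random.
- **What families hear.** Section {26a} has enumerators confirm that parents understand how the product will reach them. It names all three routes, including monthly voucher redemption.
- **Analysis set.** Section {20a} limits the intention-to-treat population to recruited households that received at least one product.

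**The concern.** Randomising clusters protects the comparison only if the people who enter each cluster's cohort do so independently of the arm. Here the recruiting team may know the channel, and families may know it too. Three steps stay open to influence after a household has been drawn at random: whether the family agrees, how hard staff try to reach it, and judgements at screening such as freedom from other serious illness.

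The trial sets out to estimate a difference between channels, with no formal test. If families who decline because of the channel have a different malaria risk from those who accept, part of the estimated hazard ratio reflects who was enrolled. A larger sample does not remove such an error, and the 90% interval does not reflect it. Adjustment for age, gender, household type and cluster size corrects only what those variables capture, which need not include motivation or exposure.

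This is not detail left to another document. The article itself places the draw after allocation and the disclosure before recruitment.

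**Working it through.** **Step 1. Is the disclosure needed by recruiters?** The stated reason is to set up voucher distribution points and recruit VHT members. In the voucher arm the first month's product is brought to the home by staff, and enrolment takes about one month, so redemption points come into use later. The reason covers the staff doing the set-up. It does not cover those who take consent and screen.

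**Step 2. What randomness already protects.**

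| Step | Chosen at random? | Can depend on the arm? |
|---|---|---|
| Household drawn | Yes | Not through the draw itself |
| Replacement drawn | Yes | Not through the draw itself |
| Child selected | Yes, by tablet | Not through the selection itself |
| Family agrees or refuses | No | Yes |
| Effort to make contact | Not stated | Yes |
| Eligibility judgement | No | Yes |

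**Step 3. The plan's own precision, as a yardstick.** Inputs from Sample size {14}: 16 clusters per arm, 40 households per cluster, 10% loss (36 followed), between-cluster coefficient of variation 0.40, 0.5 to 1 infection per person-year, 12 months. The 90% level is from section {20a}.

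First infections per cluster: E = 36 × (1 − exp(−rate)). Standard error of the log hazard ratio: SE = √[(2/16) × (1/E + 0.40²)].

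- Rate 0.5: E = 14.2, SE = 0.170, limits exp(±1.645 × 0.170) = 0.76 to 1.32.
- Rate 1.0: E = 22.8, SE = 0.160, limits exp(±1.645 × 0.160) = 0.77 to 1.30.

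The article gives lower limits of 0.75 to 0.77 and upper limits of 1.30 to 1.33, so its figure is reproduced. With t on 30 degrees of freedom the limits at rate 0.5 are 0.75 to 1.33. The half-width on the log scale is 0.26 to 0.28.

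**Step 4. Illustration of bias (all inputs assumed).** Suppose a share d of households is lost in one operational arm only and replaced by consenters. Let decliners have RR times the incidence of consenters, with no true channel difference and no adjustment. The complete arm has mean incidence (1 − d) + d × RR relative to consenters, and the depleted arm has 1. The spurious hazard ratio is 1/(1 − d + d × RR).

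| d | RR = 0.5 | RR = 2 |
|---|---|---|
| 10% | 1/0.95 = 1.05 | 1/1.10 = 0.91 |
| 20% | 1/0.90 = 1.11 | 1/1.20 = 0.83 |

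**Step 5. Compare.** |ln 0.83| is about 0.18, roughly two thirds of the half-width (0.18/0.28 = 0.64; 0.18/0.26 = 0.69). ln 1.11 is about 0.10, or about 0.4 of it. All four results lie inside the plan's interval, and the direction depends wholly on whether decliners are at higher or lower risk.

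**The case against.** The defence is substantial. The listing preceded allocation, and households, replacements and children are all selected at random, so staff do not choose whom to enrol. A random draw made after allocation is not biased for that reason alone. Every arm gets the product, a net and free malaria treatment, so there is no untreated arm to refuse. The article puts participant time at about 1 hour in the voucher arm against 50 minutes in the others. Redemption points lie within the cluster and are chosen by its community. Large refusal because of the channel is therefore not obvious. All of this stands, and it narrows the point to consent, contact and screening.

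A reader might infer more, but the documents do not support it:

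- *Unblinded staff handle absent or refusing households at their discretion.* The article is silent on this and refers to standard operating procedures.
- *People who know the arm draw the replacements.* The article does not say who draws them.
- *An Excel draw cannot be audited.* Such a draw can be saved and frozen, and the text does not say whether it was.
- *Only households with a child at home are approached.* The phrase may equally mean that a child lives there.
- *The bias would flatter the voucher channel.* That needs decliners to be at higher risk. Lower-risk decliners push the hazard ratio the other way.

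Full concealment is also not achievable. Voucher communities help choose distribution points, and VHT members are recruited inside VHT clusters.

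**Conclusion.** The point holds as a weakness in the stated sequence. Recruitment follows disclosure, the stated reason for disclosure does not extend to enrolment staff, and the text does not withhold the channel from them or from families. The cohorts can therefore differ at baseline. The documents do not show that they will.

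No refusal or contact figures are given, so neither size nor direction can be computed. Under the assumptions in the working (10-20% loss in one arm only, relative incidence 0.5 to 2, no adjustment), the hazard ratio would be multiplied by about 0.83 to 1.11. It would go too far to say that the bias is as large as the difference under study. The plan's interval describes precision at a hazard ratio of 1 and is not an effect size. Certainty is high for the order of events and low for the amount of bias. This is a low-cost improvement to make and does not invalidate the design.

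**What to change.** 1. **Sequence generation {16a} and Enrollment of the cohort.** Someone working on cluster codes without arm labels generates one seeded random order per cluster of all listed households with an age-eligible child, and locks it before fieldwork. Staff approach the first 45 and take replacements strictly in that order. The same fixed number of return visits applies in every arm before a household is passed over.
2. **Concealment mechanism {16b}.** Limit disclosure before enrolment to staff who set up distribution points or recruit VHT members. Other existing staff enrol in those clusters.
3. **Consent {26a}.** Use the same wording in all arms, since the text already names all three channels. Where feasible, confirm a household's own channel only after consent, screening and the baseline rapid test are recorded.
4. **Statistical methods {20a}.** If step 3 is adopted, analyse enrolled children as randomised whether or not a first product was received. Otherwise families who withdraw on learning their channel drop out of the intention-to-treat set, and the selection only moves to a later step. Section {26a} uses data only up to withdrawal, so these families add little follow-up, but they remain counted.
5. **Reporting.** Give approached, absent, refused, ineligible and replaced households, and baseline rapid-test prevalence, by arm.

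The cost is a short script, a reserve list, one consent text and some reassignment of staff, with no extra participants. The downsides are a few withdrawals once the channel is known and incomplete concealment in voucher and VHT communities. Enrolment was planned for July to August 2024. If it is over, steps 1 to 3 can no longer be applied, but the reporting in step 5 and a statement of the risk still can.
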